**Figure 1 F1:**
[figure not shown]
Overview of study design.

Further, we will use well-tested data collection methods, training, and supervision to ensure intervention fidelity and biochemical verification of smoking status. The overall study protocol has been approved by the University of Illinois at Chicago Institutional Review Board (Protocol # 2020-0532). Aim 1 of the study was determined to be exempt due to the lack of human subject involvement (Protocol #2020-1621). Aim 2 was determined to be exempt from IRB approval due to minimal risk (Protocol #2021-0578). However, informed consent will be obtained from all study participants in this aim. Each aim of the study will be reviewed and approved by the IRB committee and informed consent obtained from participants in each of the aims determined by the IRB to represent human subjects research. The study funding period and study timeline will take place between June 2020-May 2023.

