All English-speaking adult patients at three MSHC locations (Main, South Shore, and Englewood) who smoke and are enrolled in the UI Health Patient Portal will be eligible for this pilot test. An equal number of patients (total *N* = 100) will be randomly selected from each location for the feasibility trial using a software program developed by programmers at the University of Illinois at Chicago. Human subject approval will be obtained before data collection, and formal informed consent obtained from participants.

Figure 3 displays an overview of the activities to be conducted in Aim 4 of the study. The intervention will be based on the 3 A's framework (Ask-Advise-Refer, [AAR]) (9, 11, 12). In the first phase of this aim, we will *Ask and Identity, All Smokers*. Project staff will review the electronic health record of the six participating clinic locations to identify all current smokers. Any patient without documented smoking status will be flagged for input during the subsequent clinical encounter. Next, we will *Advise a Quit Attempt*. A random selection of all smokers enrolled in the patient portal will be sent a signed letter from their provider via the portal. The letter will describe health risks associated with smoking, explain the availability of free treatments, strongly encourage the patient to make a quit attempt, and inform them that they will be receiving a call from the Illinois Tobacco Quitline. Patients will be informed that the ITQL will provide free smoking cessation counseling and nicotine replacement therapy (nicotine patches). An automated text or email message with a hyperlink to the portal login page will be generated and sent to patients to alert them of the message from their providers.

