### Data Analysis

Consistent with RE-AIM (32), our primary outcomes will include Reach and Impact (Reach x Efficacy). We will obtain feasibility data from the patient portal. First, we will assess which patients received (opened) an electronically generated message from their providers advising them to make a quit attempt, describing free stop smoking services from the ITQL, and informing them about an upcoming call from the ITQL. All patients will be allowed to opt into the proactive ITQL counselor call. We will evaluate what percentage of patients opt-in to treatment and the demographic factors associated with the decision to accept linkage to the ITQL. Next, we will assess the percentage of patients who opted-in to treatment and were subsequently reached by the ITQL. Finally, we will evaluate the percentage of patients who engaged in stop smoking treatment (participated in more than 1 counseling call) and their quit outcomes. Patient receipt of treatment and self-reported quit rates will be obtained from the ITQL. The ITQL will provide a monthly report on patient engagement and quit rates. Statistical analyses (multivariable logistic regression models) will be conducted to determine demographic factors (age, race, gender, clinic) associated with receipt of the provider message and advice to quit smoking, receipt of treatment by the ITQL, and quit rates. One of our smoking cessation patient navigators will contact patients who opted-in to linkage to the ITQL and who were not reached by an ITQL counselor. Patient navigators will record barriers to quitline engagement that will be qualitatively analyzed. Data from this aim will refine implementation strategies and procedures in preparation for a fully powered randomized controlled trial.

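### Biochemical verification is promised but quit rates are described as quitline self-report, and the primary Impact outcome does not fix which step counts as Reach

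*Protocol article*

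**What the plan says.** **How smoking status is ascertained.** The Study Design text of the protocol article (the paragraph after Figure 1) lists data collection methods, training and supervision meant "to ensure intervention fidelity and biochemical verification of smoking status". In Data Analysis the source of the quit outcome is different: "Patient receipt of treatment and self-reported quit rates will be obtained from the ITQL". The route is also given: "The ITQL will provide a monthly report on patient engagement and quit rates". No other source of quit data is named for Aim 4.

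**Whose quit outcome is described.** Data Analysis follows patients through a sequence: letter opened, call accepted, reached by the ITQL, engaged. Quit outcomes appear at the last step, as the "percentage of patients who engaged in stop smoking treatment (participated in more than 1 counseling call) and their quit outcomes". Quit rates come up once more, in the list of logistic regression outcomes ("receipt of treatment by the ITQL, and quit rates"), without a denominator.

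**What depends on it.** Data Analysis states: "our primary outcomes will include Reach and Impact (Reach x Efficacy"). It does not say which step of the sequence is Reach. The Aim 4 sample is fixed in Study Procedures: "An equal number of patients (total *N* = 100) will be randomly selected from each location for the feasibility trial".

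**The concern.** There are two separate problems.

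First, verification is presented as a mark of rigor, but the only ascertainment the article describes is what patients tell the service that treats them. A reader of Study Design would take the quit rate to be verified; a reader of Data Analysis would not.

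Second, a product of Reach and Efficacy is a population quit rate only if both factors meet at the same step. Efficacy is described among patients with more than one call. Reach could be any of four steps. If it is set at an earlier and larger one, Impact credits the quit rate of engaged patients to patients who never engaged.

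The Conclusions section says that the study will give initial data on Reach and Effectiveness ahead of a fully powered randomized trial. An unverified rate read as verified, or a mismatched product, could carry into the planning of that trial.

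**Working it through.** The article gives no power, effect size or expected quit rate for Aim 4, so there is no figure of its own to reproduce. The check is a comparison of the text, followed by an illustration of how much the denominator matters.

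**Step 1: is a verification step described anywhere?**

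- Aim 1: de-identified health-record status (current, former, never). No sample.
- Aim 2: focus groups and interviews. No sample.
- Aim 3: portal enrollment counts. No sample.
- Aim 4: portal letter, quitline telephone counseling and navigator calls. Navigators record barriers to engagement, not abstinence. No sample, marker, cutoff or time point.
- Data Analysis: self-report through the ITQL.

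The claim in Study Design has no counterpart in any described procedure.

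**Step 2: when does Reach x Efficacy equal the population quit rate?**

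Let N be the patients selected, e the proportion with more than one call, q the proportion of those who quit, and r the proportion at whichever step is called Reach. Patients with no ITQL quit record are counted as not quit.

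- Quits = N x e x q
- Quit rate over all selected = e x q
- Impact = r x q
- Impact divided by the all-selected rate = r / e

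The ratio is 1 when r = e. It exceeds 1 when Reach is counted at an earlier, larger step.

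**Step 3: illustration.**

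Inputs:

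- N = 100 (Study Procedures, Aim 4).
- q = 12.7% with counseling and 28.1% with counseling plus nicotine replacement (Tobacco Cessation Treatments).
- e = 12.8% to 14.5%, borrowed from the Introduction's figures for receiving counseling or medication after outreach in other trials. Using this for more than one ITQL call is an assumption.
- e = 30% and 50% are further assumptions, to show the range.

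| e | Engaged of 100 | Quits at q = 12.7% to 28.1% | Rate over all 100 | Rate among engaged |
|---|---|---|---|---|
| 12.8% | 12.8 | 1.63 to 3.60 | 1.6% to 3.6% | 12.7% to 28.1% |
| 14.5% | 14.5 | 1.84 to 4.07 | 1.8% to 4.1% | 12.7% to 28.1% |
| 30% | 30 | 3.81 to 8.43 | 3.8% to 8.4% | 12.7% to 28.1% |
| 50% | 50 | 6.35 to 14.05 | 6.4% to 14.1% | 12.7% to 28.1% |

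The engaged-only rate would also be imprecise. In whole patients, 2 quits of 13 has an exact 95% interval of 1.9% to 45.4%, and 4 of 13 has 9.1% to 61.4%. Over all 100, 2 quits gives 0.2% to 7.0% and 4 quits gives 1.1% to 9.9%.

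**Step 4: matched and mismatched products.**

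- Matched, r = e = 14.5%: 0.145 x 0.281 = 4.1%, the same as the all-selected rate.
- Mismatched, with Reach counted as letters opened at an assumed r = 60%: 0.60 x 0.281 = 16.9%. The ratio r / e is 0.60 / 0.145 = 4.1 at 14.5% engagement, 0.60 / 0.30 = 2.0 at 30%, and 0.60 / 0.50 = 1.2 at 50%.

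**Step 5: what verification could change.**

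The article gives no misreporting rate. If 10% to 40% of reported quits were not confirmed (assumed range), 12.7% would fall to between 11.4% (12.7 x 0.90) and 7.6% (12.7 x 0.60), and 28.1% to between 25.3% and 16.9%.

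**The case against.** **On verification.** Data Analysis names self-report but does not say that it is the only source; self-report followed by confirmation of claimed quits would be consistent. The Ethics Statement says that Aims 3 and 4 had not begun and that their protocols would go to the review board separately, so a sampling step may stand in a document not shown. This stands against any claim that verification has been dropped. It does not remove the need to reconcile the two statements, because the article itself names self-report as the source.

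**On the denominator.** A reader might infer that patients who did not open the letter, declined, were not reached or stopped after one call are excluded from the quit rate. The article does not say so. The regression sentence gives no denominator, and an all-selected analysis is not ruled out. Coding of missing quit status is also commonly left to an analysis plan. What remains is that the only group for which quit outcomes are described is the engaged.

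**On Impact.** A reader might infer that Impact is inflated by construction. It is not: multiplying Reach by efficacy among those reached is a legitimate definition, and with matched steps it returns the all-selected proportion. Overstatement follows only if the steps differ, which the article neither states nor prevents.

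**On other data.** Health-record smoking status from Aim 1 is to serve as secondary endpoints for tracking the intervention, and does not depend on quitline contact. It is de-identified, and no link to the Aim 4 patients is described, so it does not replace the ITQL quit rate.

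**On size.** The engagement figures come from other trials and another measure. Aim 4 patients are portal users who consent, and navigators follow up non-responders, so engagement could be much higher. A large fold-difference between the two rates is simply the inverse of the assumed engagement rate and is not evidence about this study.

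**Conclusion.** The point holds at moderate severity. As written, the quit outcome does not have the verified quality that Study Design claims for it; this rests on the text alone. The definition of the primary Impact outcome is incomplete in a way that matters, because the step counted as Reach is not tied to the step at which quit outcomes are described.

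The size cannot be known from the article. On the borrowed rates, the same quits are 1.6-4.1% of all selected patients and 12.7-28.1% of the engaged; at an assumed 50% engagement the gap narrows to 6.4-14.1% against 12.7-28.1%. These figures assume no recorded quits outside the engaged group.

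The documents do not support saying that verification has been abandoned, that unengaged patients will be excluded, or that Impact will be inflated. Nor do they support a higher severity: Aim 4 is a feasibility pilot of 100 patients with no stated efficacy test, and the article leaves confirmation to a later trial.

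**What to change.** 1. Reconcile Study Design with Data Analysis. Remove the verification claim and label the outcome self-reported abstinence from the ITQL. If the Aim 4 protocol already contains a verification step, describe it in Data Analysis instead.
2. Name the step that counts as Reach, and make it the step that defines the Efficacy denominator. Impact may stay a product.
3. Report quits over all 100 selected patients, with patients who have no ITQL quit record counted as not quit. Show the engaged-only rate beside it, labelled as such.

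The cost is wording and one extra line in the results table; removing the claim and relabelling the outcome require no new procedure. The downside is that the headline quit rate becomes less favorable.

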### Theoretical Model

Mi QUIT CARE is informed by the Centers for Disease Control's Socioecological Model (SEM) (29) and cognitive-behavioral theories (33). The University of Illinois (UI) Cancer Center and MSHC have experience conducting multi-level interventions to reduce cancer-related disparities (34). Guided by the SEM (29), the UI Cancer Center has proposed a new pathway in reducing pulmonary health inequalities. At the *individual level* and consistent with prior research, cognitive-behavioral models of behavior change (i.e., Theory of Planned Behavior) (33) will be used to understand attitudes toward smoking cessation among patients at FQHCs. *Interpersonal interventions* will include patient navigators to support patient uptake of the patient portals and address barriers to receiving evidence-based tobacco cessation treatments. We will evaluate a system-wide smoking cessation intervention delivered via a patient health portal at the organizational level. *Community-level support* is fostered through ongoing partnerships with organizations like the American Lung Association and the Illinois Tobacco Quitline. Lastly, at the *policy level*, the UI Cancer Center acknowledges the role of policy in improving pulmonary health outcomes, such as the regulation of flavored tobacco products, including mentholated brands (35, 36) (see Figure 2).

**Figure 2 F2:**
[figure not shown]
UICC adapted socioecological framework.

### Setting

This multi-level intervention will be delivered via the University of Illinois Hospital and Health Sciences System (UI Health) Patient Portal, a cost-effective and sustainable intervention delivery system. Mi QUIT CARE will be conducted in six Mile Square Health Center (MSHC) clinics, a network of 13 community-located FQHCs, including school-based health centers. MSHC is co-owned and operated by UI Health. MSHC serves communities experiencing a high burden of pulmonary health morbidity and mortality associated with tobacco use. The majority of MSHC patients are Black (74%), live at or below the federal poverty level (98%), and are insured through Medicaid (55%, 10% are uninsured). MSHC has the infrastructure to complete the study and monitor the impact of the intervention on their patients' smoking and pulmonary health status over time. Metrics demonstrating implementation readiness include: (1) consistent assessment and documentation of smoking status in the electronic health record by providers; (2) current availability of a system-wide patient portal that can be used to communicate with patients regarding their care; (3) an established collaboration with the Illinois Tobacco Quitline as part of an existing smoking cessation program at MSHC, and (4) an existing patient navigation program for smoking cessation and lung cancer screening.

### Stakeholder Engagement

Community engagement is essential to the development of effective interventions. As shown in Table 1, we have assembled a diverse community advisory board representing multiple engagement levels across the socioecological model (29). Engaging community stakeholders is essential to developing tailored tobacco cessation interventions for at-risk populations (37). Specifically, community engagement will help to ensure: (a) the smoking cessation intervention is informed by and responsive to stakeholder needs; (b) the implementation of evidence-based interventions that align with patient preference and clinic culture; (c) the sustainability and scalability due to iterative stakeholder input; and (d) broad dissemination of findings to local, regional and national organizations (37). The community advisory board will meet quarterly throughout the project and will help to ensure the appropriateness of methods used.

**Table 1 T1:** Mi CARE QUIT community advisory board.

**Level of engagement**	**Stakeholder name or entity**
Policy	American Lung Association Illinois Tobacco Quitline Chicago Department of Public Health American Cancer Society
Community	American Lung Association Illinois Tobacco Quitline Chicago Department of Public Health
Organizational	Providers at MSHC American Lung Association Illinois Tobacco Quitline Chicago Department of Public Health American Cancer Society
Interpersonal	Patient Navigators Implementation and Dissemination Specialist Providers
Individual	Current and former smokers who are patients at MSCH

### Study Procedures

Below is a description of study procedures, separated by study aims.

*Aim 1: Examine the burden of tobacco use (smoking prevalence) and its influence on pulmonary health inequalities (lung cancer, COPD, and asthma) in the patient populations served by MSHC*.

Patient-level data from the electronic health records (EHR) of all six MSHC locations will be analyzed to evaluate the burden of tobacco use in our patient population. MSHC utilizes the epic platform for their EHR and can extract de-identified patient-level data. Eligibility criteria for inclusion in the analyses include (1) age 18 years and older, (2) a patient at one of the six participating MSHC clinics, and (3) having received care at MSHC within the past 2 years. Patient-level demographic data include age, gender, race/ethnicity, education, income status, relationship status, insurance type, and zip code. Smoking data include current smoking status (current, former, never). Smoking-related lung conditions to be examined include a diagnosis of lung cancer, COPD, and asthma. Chronic health conditions are exacerbated by smoking, including HIV infection, high blood pressure, cardiovascular disease, stroke, asthma, and diabetes. The data manager will prepare a request for the data sets, and the study biostatistician will analyze data to characterize the burden of tobacco use on pulmonary health outcomes. Prevalence, comparisons across clinic locations, and associations (e.g., race/ethnicity, gender, age) will be examined. Data from this aim of the study will allow us to establish a baseline level of smoking among the patient population and the presence of smoking-related comorbidities among patients who smoke. These data will serve as secondary endpoints in tracking the progress of our tobacco cessation intervention. No human subjects are involved in this aim.

*Aim 2: Evaluate among MSHC patients and providers, knowledge, attitudes, barriers, and facilitators related to smoking cessation, engagement with the tobacco quitline, linkage to the tobacco quitline via a patient health portal, and receipt of patient navigation to facilitate access to the tobacco quitline*.

A qualitative design will obtain stakeholder input on the interventions to test Mi QUIT CARE. Five focus groups (*N* = 50) will be conducted with current smokers, and in-depth interviews will be conducted with providers at MSHC (*N* = 24). The goals of the qualitative interviews will be to understand knowledge, attitudes, beliefs, and barriers related to (1) smoking cessation, (2) engagement with the quitline, (3) linkage to the quitline via the UI Health Patient Portal, and (4) the acceptability of patient navigation to facilitate enrollment in the patient portal and address barriers to engaging with the quitline. Eligibility criteria for focus groups include: (1) aged 18 years and older, (2) current smoker, (3) English speaking, and (4) ability to provide informed consent. Eligibility criteria for providers include: (1) employed at MSHC and (2) providing primary care for adults. All study participants will be recruited from MSHC via posted flyers and clinic-based recruitment activities conducted by trained research assistants.

Focus groups (90 min) and individual interviews (45 min) will be conducted according to standardized methodology, including using trained moderators, a moderator's guide, post-session debriefings, and a review of transcribed audiotapes (38). The moderator's guide for the focus groups and in-depth interviews will be developed based on cognitive-behavioral models of health behavior change. Questions will include knowledge, attitudes, perceived social norms, perceived risks and benefits, self-efficacy, and barriers and facilitators regarding receipt of smoking cessation treatment and the use of the patient portal. Focus group participants will also complete a brief demographic survey. Interviews will be analyzed according to the methods of framework analysis (39). We expect to reach saturation with the proposed sample sizes based on our prior experience (40–43). NVivo will be used for qualitative data management and analyses. First, focus groups and in-depth interviews will be analyzed based on study questions and additional sub-themes identified. These design and analytic approaches are appropriate for applied research (39). The information obtained from patients and providers will help us understand initial attitudes and opinions about the intervention approaches and help refine intervention-related strategies.

Based on focus group data, we will partner with health literacy experts to tailor project informational materials to the needs of patients with low levels of health and technology literacy. Informational materials will include information about enrollment and use of the patient portal, communication from MSHC providers advising all current smokers to make a quit attempt, smoking cessation educational pamphlets, and a description of the tobacco quitline. Materials will be tailored to the needs of low-income patients in terms of language, health literacy, and health beliefs. In addition, tailoring of patient educational materials will be on Kreuter's methods for cultural tailoring (38) and will include (a) peripheral (images, etc. salient to smokers); (b) evidential (cancer rates specific to smoking); (c) linguistic (language and terms used by group); (d) constituent-involving (involving diverse populations of smokers); and (e) sociocultural tailoring (including cultural beliefs). After tailoring materials, a new sample of smokers (*N* = 25) and providers (*N* = 10) will be recruited based on the above eligibility criteria. In-depth interviews will collect data on the usability, acceptability, and comprehension of tailored educational materials. A trained research assistant will review materials with individual participants (30 min). The talk-aloud approach (44) will be used to obtain users' feedback. All sessions will be audiotaped, and information reviewed to make suggested changes and to finalize educational materials. All participants will receive a stipend. This aim was deemed exempt from IRB approval due to the low potential risk for participant harm. However, standard information materials will be provided and informed consent obtained before data collection. The information obtained from patients and providers will support the development of the patient portal strategies to increase the intervention's usability, acceptability, and cultural appropriateness.

*Aim 3: Evaluate the use of community engagement strategies to increase uptake of the Patient Portal*.

The utility of patient health portals as a health promotion delivery system will be limited if uptake is low among patients in FQHC who may have issues with general literacy, health literacy, and technology-based literacy levels. In this aim, we will evaluate a tailored multi-modal educational campaign to increase the enrollment of MSHC patients in the UI Health Patient Portal. Currently, only 1% of MSHC patients are enrolled in the patient portal. The goal is to increase enrollment to 40% across the 3 years of the developmental trial to demonstrate the feasibility of delivering Mi QUIT CARE *via* the patient portal. The educational campaign will occur in three MSHC locations (Main, South Shore, and Englewood). The remaining three locations (Back-of-the-Yards, Cicero, and Humboldt Park) will serve as waitlist controls. The following strategies will be used to increase enrollment: (1) branding of the outreach initiative, “*My UI Health”*; (2) conducting a clinic campaign using materials tailored to low health literacy populations; (3) offering written provider recommendation and enrollment information during all clinical encounters; (4) mailing informational letters to all MSHC patients that includes enrollment instructions; and (5) offering onsite enrollment assistance provided by patient navigators. Trained patient navigators will assist clinic patients in enrolling in the patient portal *via* kiosks and secure iPads. After the data collection phase, the patient enrollment campaign will be conducted at the three waitlist control clinics.

Study investigators will first evaluate patient portal enrollment considering all patients aged 18 and older who have had an office visit during the previous 24-month period to establish a baseline comparator. During the campaign, enrollment rates will be examined for each clinic to monitor increases in enrollment in the patient portal during the campaign period. We will compare enrollment rates for the intervention clinics vs. the control clinics. Further, we will evaluate whether additional targeted outreach efforts are needed for some patient groups by analyzing whether demographic factors (age, education, gender, race/ethnicity, last provider visit) are associated with portal enrollment. In addition, we will collect reasons for refusal among patients approached in the clinics by patient navigators. Data on enrollment will establish the feasibility of population-based engagement of health promotion interventions via the patient portal. Informed consent will not be required as this aim is part of a quality improvement project at the clinic to increase access to the patient portal. All analysis of portal uptake will be based on de-identified data.

*Aim 4: Test the acceptability, feasibility, and capacity of MSHC FQHC to deliver Mi QUIT CARE*.

We propose a Hybrid Type I effectiveness-implementation design grounded in RE-AIM (32). Hybrid I types are appropriate for evaluating outcomes associated with clinical intervention and implementation strategies (45). Led by our informatics team, our web application development will be spread across three phases: design, production, and testing/deployment. During the design phase of the study, our technical teams will work closely to refine and document all system specifications and requirements. System logic/rules will be generated. Wireframes, storyboards, interface mock-ups, schematics, and database designs will be produced. In the production phase, the technical team will build the application's site and database. The process will conclude with the testing and deployment phase in which the study and technical teams pass through multiple cycles of quality assurance. After the system is deployed to the live environment, the study and technical teams will stay engaged over the project's lifespan.

All English-speaking adult patients at three MSHC locations (Main, South Shore, and Englewood) who smoke and are enrolled in the UI Health Patient Portal will be eligible for this pilot test. An equal number of patients (total *N* = 100) will be randomly selected from each location for the feasibility trial using a software program developed by programmers at the University of Illinois at Chicago. Human subject approval will be obtained before data collection, and formal informed consent obtained from participants.

Figure 3 displays an overview of the activities to be conducted in Aim 4 of the study. The intervention will be based on the 3 A's framework (Ask-Advise-Refer, [AAR]) (9, 11, 12). In the first phase of this aim, we will *Ask and Identity, All Smokers*. Project staff will review the electronic health record of the six participating clinic locations to identify all current smokers. Any patient without documented smoking status will be flagged for input during the subsequent clinical encounter. Next, we will *Advise a Quit Attempt*. A random selection of all smokers enrolled in the patient portal will be sent a signed letter from their provider via the portal. The letter will describe health risks associated with smoking, explain the availability of free treatments, strongly encourage the patient to make a quit attempt, and inform them that they will be receiving a call from the Illinois Tobacco Quitline. Patients will be informed that the ITQL will provide free smoking cessation counseling and nicotine replacement therapy (nicotine patches). An automated text or email message with a hyperlink to the portal login page will be generated and sent to patients to alert them of the message from their providers.

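### Aim 1's clinic-wide smoking and comorbidity data are named as secondary endpoints of an intervention offered to at most 100 patients, so a change in them could not be attributed to it

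*Protocol article*

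**What the plan says.** Study Procedures, Aim 1, describes an extract from the electronic health record. The clinics "can extract de-identified patient-level data". Inclusion requires age 18 or over, being "a patient at one of the six participating MSHC clinics, and (3) having received care at MSHC within the past 2 years". The purpose is to "establish a baseline level of smoking among the patient population and the presence of smoking-related comorbidities among patients who smoke", the conditions of interest including lung cancer, COPD and asthma. The article then adds: "These data will serve as secondary endpoints in tracking the progress of our tobacco cessation intervention".

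Aim 4, in the same section, defines who can receive the intervention. Adults who speak English and attend "three MSHC locations (Main, South Shore, and Englewood) who smoke and are enrolled in the UI Health Patient Portal will be eligible". The number is fixed: "An equal number of patients (total *N* = 100) will be randomly selected from each location for the feasibility trial". Aim 4 also has staff review the records of all six clinics to find smokers, and states: "Any patient without documented smoking status will be flagged for input during the subsequent clinical encounter".

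The Setting section says that providers already assess and record smoking status consistently, that a cessation program exists, and that the clinics can monitor the intervention's impact on smoking and pulmonary health over time. The Data Analysis section names Reach and Impact as primary outcomes and takes quit rates from the quitline. It does not say how the Aim 1 data would be used to judge the intervention.

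**The concern.** The population measured and the population exposed do not match. The endpoint is an average over every adult patient of six clinics, while the intervention can touch at most 100 of them at three clinics. Fewer will be treated, because a patient must open the letter, accept the call and be reached. Any effect is diluted across a much larger group, and the article describes no comparison that would separate it from other changes in that group.

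The comorbidity part is weaker still. Chronic diagnoses would not be expected to shift because up to 100 people were offered cessation treatment within a study running from June 2020 to May 2023. Because comorbidity is described among patients who smoke, a patient who quits leaves the denominator and a newly charted smoker enters it.

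At stake is the reading of the result. The Conclusions say this study will give initial data on Reach and Effectiveness ahead of a fully powered randomized trial. A drift in clinic prevalence, up or down, could be taken as evidence about the intervention and carried into that trial.

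**Working it through.** The article gives no power, effect size or sample-size calculation for these endpoints, so there is no figure to reproduce. The check is a dilution calculation.

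**Inputs from the article**
- 100 selected patients (Study Procedures, Aim 4).
- Quit rates of 12.7% for quitline users and 28.1% with nicotine replacement (Tobacco Cessation Treatments).
- 25.8% tobacco use in health centers of this type (Introduction), used as a proxy because the clinics' own smoking prevalence is not given.

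**Assumptions**
- N, the number of adults in the Aim 1 population, is not given; 2,000 to 60,000 is shown.
- Two independent snapshots, each of size N, two-sided 5% level.
- All 100 selected patients are treated, which favours the plan.

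**Formulas**, with p = 0.258
- Fall in prevalence = 100 × quit rate / N.
- Change detectable with 80% power = (1.96 + 0.84) × √(2p(1 − p)/N).
- Chance of a significant fall = Φ(fall/SE − 1.96), with the SE from the two proportions.

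For N = 2,000 the fall is 28.1/2,000 = 1.41 points and the detectable change is 2.80 × √(2 × 0.258 × 0.742/2,000) = 3.88 points.

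| N | Fall at 12.7% (points) | Fall at 28.1% (points) | Detectable change (points) | Chance of a significant fall, at 28.1% |
|---|---|---|---|---|
| 2,000 | 0.64 | 1.41 | 3.88 | 17% |
| 5,000 | 0.25 | 0.56 | 2.45 | 9% |
| 10,000 | 0.13 | 0.28 | 1.73 | 7% |
| 20,000 | 0.06 | 0.14 | 1.23 | 5% |
| 40,000 | 0.03 | 0.07 | 0.87 | 4% |
| 60,000 | 0.02 | 0.05 | 0.71 | 4% |

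The fall shrinks with 1/N and the detectable change only with 1/√N, so the smallest population is the most favourable case.

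These are gross quits. Pairing the ends of the abstinence ranges that the article cites for outreach against standard practice gives 5.3 − 1.1 = 4.2 and 13.5 − 10.9 = 2.6 net quits per 100. At N = 2,000 the larger figure is 4.2/2,000 = 0.21 points.

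**Effect of completing missing smoking status.** The missing share m is not given, so it is assumed.
- If missing is counted as non-smoking, completing it at 25.8% raises recorded prevalence by m × 25.8%: 0.26, 1.29 or 2.58 points for m = 1%, 5% or 10%.
- If only documented patients are analysed, the shift is m × (prevalence among the missing − 25.8%). With m = 5% it is −0.59 points if the missing smoke at 14.1% (the national figure in the Introduction), +0.46 points at 35% (the top of the Chicago community range there), and zero at 25.8%.
- Under the first convention, the share that cancels 28.1 quits is (28.1/N)/0.258: 5.4% at N = 2,000, 1.1% at 10,000 and 0.3% at 40,000.

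The charting effect may thus be nil or may exceed the largest treatment effect. The article does not allow a choice between these.

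**The case against.** **The sentence may mean only a baseline.** The preceding sentence speaks of a baseline, the study is formative, no follow-up extract or before/after test is described, and an article may leave the computation of a secondary endpoint to a fuller document. That is a fair account of the context. But the sentence gives the data endpoint status for the present intervention, and nothing in the article confines it to a later trial. The objection here is to that role, not to missing computational detail.

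**The precision is too pessimistic.** Two-year windows on the same clinics would share many patients, so independent snapshots probably overstate the noise. At 2,000 adults there would be 516 smokers, so 100 selected patients would be 19% of them, hardly negligible. Both points stand. Greater precision would still not show what caused a change.

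**Stronger readings that do not hold.** A reader might infer that any movement in prevalence would merely reflect charting. The documents do not support that: no missing share is given, the Setting section calls documentation consistent, and an analysis of documented patients could show no shift. Secular trend, case mix and the existing cessation program are equally possible causes. The prompt concerns smoking status and does not alter diagnoses. A reader might also infer that the exposed patients cannot be followed in the records at all. That applies to the de-identified Aim 1 extract; Aim 4 patients give consent and are referred with a unique ID.

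**Conclusion.** The concern holds in this form: the Aim 1 data cannot serve as endpoints of the intervention, because a change in them could not be attributed to it. Under the stated assumptions the most favourable fall in prevalence is about 1.4 points at 2,000 adults and 0.05 at 60,000, below the detectable change at every size examined; the chance of a significant fall is at most about 17%. Those figures rest on an assumed clinic size, a proxy prevalence and independent snapshots. The attribution problem depends on none of them. The charting prompt is one possible source of change that the plan itself introduces, of unknown size. The primary outcomes, the selection of patients and the quitline-reported quit outcomes are unaffected, so this is a correction to a secondary endpoint and not a flaw in the pilot as a whole.

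**What to change.** Replace the endpoint sentence under Aim 1 with one along these lines: the Aim 1 data are a descriptive baseline of smoking and smoking-related conditions in the clinic population and are not endpoints of the intervention. Take any secondary cessation endpoint from the consented Aim 4 patients, with all selected patients in the denominator.

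If clinic prevalence is still shown over time, restrict it to patients with smoking status documented at both times, report the share with missing status, and label the display descriptive. That restriction needs the two extracts to be linkable by a stable code, or applied before de-identification.

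The new wording should not call the Aim 1 extract the sampling frame for Aim 4: the extract is de-identified, and Aim 4 finds smokers through its own record review.

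The cost is a sentence or two of text and the loss of a nominal secondary endpoint that carries almost no information about the intervention. The baseline description keeps its full value.
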